## Abstract

**Background:** Artificial intelligence-based software may automatically detect ischaemic stroke lesions and provide an Alberta Stroke Program Early CT score (ASPECTS) on CT, and identify arterial occlusion and provide a collateral score on CTA. Large-scale independent testing will inform clinical use, but is lacking. We aim to test e-ASPECTS and e-CTA (Brainomix, Oxford UK) using CT scans obtained from a range of clinical studies.

**Methods:** Using prospectively collected baseline CT and CTA scans from 10 national/international clinical stroke trials or registries (total >6600 patients), we will select a large clinically representative sample for testing e-ASPECTS and e-CTA compared to previously acquired independent expert human interpretation (reference standard). Our primary aims are to test agreement between software-derived and masked human expert ASPECTS, and the diagnostic accuracy of e-ASPECTS for identifying all causes of stroke symptoms using follow-up imaging and final clinical opinion as diagnostic ground truth. Our secondary aims are to test when and why e-ASPECTS is more or less accurate, or succeeds/fails to produce results, agreement between e-CTA and human expert CTA interpretation, and repeatability of e-ASPECTS/e-CTA results. All testing will be conducted on an intention-to-analyse basis. We will assess agreement between software and expert-human ratings and test the diagnostic accuracy of software.

**Conclusions:** RITeS will provide comprehensive, robust and representative testing of e-ASPECTS and e-CTA against the current gold-standard, expert-human interpretation.

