## Methods

### Study design

We will test the accuracy of e-ASPECTS and e-CTA software for the automated assessment of CT scans performed acutely for suspected stroke among representative patients. We will compare e-ASPECTS/e-CTA with expert human readers who form the current reference standard. We will use CT scans from acute stroke trials that include a range of commonly encountered scan appearances including early ischaemia, haemorrhage, typical pre-stroke features and mimics. All scans have been rated by panels of experts representing many different individuals across these non-commercial trials. We will in addition, perform new human-ratings for a subgroup of the previously collected scans to compare the time needed for human versus e-ASPECTS assessment of CT and to assess the clinical impact of e-ASPECTS software on acute stroke care, i.e. whether it influences diagnostic confidence or alters treatment decisions.

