### Sample size considerations

Tests of diagnostic accuracy are difficult to power and benefit from maximising the sample size^33^. In addition, sample size calculations may be inappropriate in this setting^34^. We therefore aim for the largest representative sample possible within available resources. However, to allow direct comparison with previous work, we estimated that to confirm that e-ASPECTS software is non-inferior for an “MCC (Matthews Correlation Coefficient) better than random” (to expert human calculation of ASPECTS using an MR diffusion-weighted imaging reference standard: e-ASPECTS correlation 0.44 versus 0.38 for experts), based on 34 patients^35^, requires a sample size of 494 scans – at 5% non-inferiority limit with 80% power and at 5% significance level. Therefore, we have set the minimum sample size for our primary outcome at 500 unique patient CT brain scans. Up to 31% of scans may fail to give an e-ASPECTS result for technical reasons^36^, therefore we will inflate the minimum sample to 725 scans (i.e. 1/0.69 × 500) to ensure the successfully processed sub-sample includes the requisite minimum 500 scans. However, this minimum will have limited power for subgroup analyses (e.g. on pre-stroke brain changes, by age or stroke severity strata) and the study cited for our power calculation used individual ASPECTS regions rather than individual patients to power their analysis, which due to lack of independence between individual ASPECTS regions, may be flawed^35^. Therefore we will process every available scan to derive the largest possible sample for testing.

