## Statistical analysis

### Analysis principles and general considerations

Primary and where appropriate, secondary outcome testing will be conducted on an ‘intention-to-analyse’ basis irrespective of whether scan processing was successful or not◦ Processing will be considered successful when an ASPECTS (0-10) or CTA result (occlusion/no-occlusion or scalar collateral score) is provided, or when arterial hyperattenuation or haemorrhage is detected.◦ We will record all software failures whether these occur at the scan upload, scan processing, or results output stage.We will use mean (standard deviation, SD) or median (inter-quartile range, IQR) to represent the distribution of parametric and non-parametric data, respectively. We will use n (%) for categorical data.Where possible, we will use diagnostic accuracy statistics as the principal method in RITeS for comparing software and expert human results. With expert human results as the reference standard, we will calculate true/false positive/negative cases (TP, FP, TN, FN, respectively) and derive sensitivity (TP/TP+FN), specificity (TN/TN+FP), positive predictive (TP/TP+FP), negative predictive (TN/TN+FN), and accuracy (TP+TN/TP+TN+FP+FN) percentages as standard. We will calculate 95% confidence intervals for each using the Wilson score method^37^. ◦ For all diagnostic accuracy testing we will include random-effects meta-analysis modelling of individual patient data (i.e. a one-step meta-analysis) to provide overall estimates of sensitivity and specificity, to assess variation within and between the 10 RITeS studies, and to account for clustering of individual study results^38^,^39^.◦ For each of the 10 RITeS studies, we will use the PROBAST method for assessing risk of bias in diagnostic modelling^40^. For all comparisons of software and expert human results, we will review side of affected brain data to ensure ASPECTS and CTA results are correctly matched for each cerebral hemisphere, i.e. matched results require same score and side. We will separately test whether knowledge of affected side impacts the accuracy of e-ASPECTS results, see secondary outcomes below.Bland-Altman plots^41^ will be used to visually compare software and expert human results, comparing mean score differences to assess the magnitude, direction and distribution of error and will use ± 1.96 SD to determine the range of agreement^42^. For software and expert human results to be considered equivalent, we will set maximum clinically acceptable limits of agreement for individual scores, specified in the relevant sections below.Krippendorff’s Alpha^43^ (K-alpha) will be used to assess reader (human-human and human-software, as necessary) agreement. K-alpha is generally more robust than kappa in this context since it can handle categorical and ordinal data, works where there is missing data, adjusts for small sample sizes, and includes multiple observers simultaneously^43^,^44^. K-alpha results are interpreted similarly to kappa with scores ranging from -1 (perfect disagreement) to +1 (perfect agreement). We will therefore also use the Landis and Koch method for interpreting K-alpha results (as commonly used for kappa): 0.00–0.20=slight agreement, 0.21–0.40=fair agreement, 0.41–0.60=moderate agreement, 0.61–0.80=substantial agreement and 0.81–1.00=almost perfect agreement^45^.Other specific statistical tests are listed in the following sections.For multivariable testing, we will check for multicollinearity between included variables by identifying variance inflation factors (VIF) >5. Where multicollinearity is detected, we will run separate (but otherwise equivalent) multivariable regression models for each of the internally correlated variables.We will not impute but will report missing data (proportions of data missing for each variable and observations not included in analyses).We will use SPSS, IBM Corporation (Armonk, USA) and/or R (https://www.r-project.org/) statistical software for all analyses. We will preferentially report 95% confidence intervals, but where appropriate, we will report p-values.

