We will classify e-ASPECTS and expert-human scores into three groups to assess diagnostic accuracy at the following clinically relevant cut-points, and present a summary (receiver-operating characteristic) ROC curve: 1) ASPECTS 10 (normal) versus ASPECTS 0-9 (abnormal)2) ASPECTS 0-7 versus 8-10^2^.3) ASPECTS 0-5 versus ASPECTS 6-10^4^.

To compare with previous work, we will use Matthews correlation coefficient (MCC), and test non-inferiority between e-ASPECTS and expert-human scores^5^,^35^. We will calculate MCC as (TPxTN)-(FPxFN)/√(TP+FP)(TP+FN)(TN+FP)(TN+FN)^46^. We will set our non-inferiority margin at 5%. Thus using the two one-sided test (TOST) procedure, we will establish non-inferiority, using the following formula: at the α=5% significance level, if the lower limit of a (1-2α) × 100% (i.e. 90%) confidence interval for the difference (e-ASPECTS minus expert-human results) is above -5%. The confidence interval is set at (1-2α) rather than the usual (1-α) because the method is equivalent to performing two one-sided tests^47^,^48^.

**
*2. Accuracy of e-ASPECTS versus expert human readers for identifying cause of stroke symptoms.*
** We will compare the diagnostic accuracy of e-ASPECTS software and expert human readers (at baseline, blind to all other clinical data including further imaging) for three groups against the reference standard, human-expert opinion using all available follow-up data including further imaging: 1) Identifying features of ischaemic stroke (including ischaemic lesions in any brain location and/or intracranial hyperattenuating arteries)2) Identifying haemorrhage, and3) Identifying any structural causes of stroke symptoms on baseline imaging (including mimics).

In addition, to aid clinical understanding and real-world applicability, we will summarise all primary outcome results using normalised frequencies. Thus we will present results as proportions of 1000 individual patients, i.e. a test sensitivity of 90% would be presented as: the test will detect disease in 900 of 1000 patients with the disease, but 100 patients with the disease will be missed by the test^49^.

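### The MCC non-inferiority test in primary outcome 1 names no reference standard; under the plan's general rule it becomes a test of near-perfect agreement with the expert

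*SAP article*

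**What the plan says.** In the SAP article, Statistical analysis, Primary outcomes, item 1, the authors state that, for comparison with previous work, "we will use Matthews correlation coefficient (MCC), and test non-inferiority between e-ASPECTS and expert-human scores". MCC is to be computed from TP, FP, TN and FN. On the margin: "We will set our non-inferiority margin at 5" per cent. Non-inferiority is concluded if the lower limit of a 90% "confidence interval for the difference (e-ASPECTS minus expert-human results) is above -5" per cent. No reference standard is named for this test.

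The rule for forming those four counts is in Analysis principles and general considerations: "With expert human results as the reference standard, we will calculate true/false positive/negative cases". The Abstract describes testing the software "compared to previously acquired independent expert human interpretation (reference standard"), and Study design says "We will compare e-ASPECTS/e-CTA with expert human readers who form the current reference standard".

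Sample size considerations takes its inputs from an earlier study that worked differently, "using an MR diffusion-weighted imaging reference standard: e-ASPECTS correlation 0.44 versus 0.38 for experts".

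A reference beyond the baseline reading, namely expert opinion informed by all follow-up data, does appear in the plan. It is named for primary outcome 2 (cause of symptoms), not for the ASPECTS comparison in outcome 1.

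**The concern.** A difference in MCC between two readers has meaning only if both are scored against the same third standard. The earlier study had one. Under outcome 1 the expert appears to be both the comparator and the standard. In that case every disagreement is counted as a software error, including any in which the software was right and the expert wrong. Software equal to or better than the experts could then be reported as having failed to show non-inferiority.

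This is the only non-inferiority test in the primary analysis, and the calculation built on it sets the minimum sample. If the reference stays unnamed, it could also be chosen after results are known.

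**Working it through.** **1. Reproduce the plan's figure.** Inputs from Sample size considerations: 0.38 for experts, 0.44 for software, margin 0.05, power 80%, significance 5%. Treating the two values as independent proportions with one-sided alpha 0.05:

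n per group = (1.645 + 0.842)² × (0.38×0.62 + 0.44×0.56) / (0.06 + 0.05)² = 6.18 × 0.482 / 0.0121 ≈ 246.3, rounded up to 247.

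Two groups give 494, an exact match. One-sided 0.025 gives 313 per group, 626 in total, and does not match. The calculation therefore uses an expert value of 0.38, which is possible only against a standard other than the expert's own reading.

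**2. Apply the stated counting rule.** MCC = (TP×TN − FP×FN) / √[(TP+FP)(TP+FN)(TN+FP)(TN+FN)]. With the expert reading as reference, the expert has FP = FN = 0. The expression reduces to TP×TN / √(TP²×TN²) = 1.

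**3. Restate the criterion.** The lower 90% limit of (software MCC − 1) must exceed −0.05, so the lower 90% limit of the software's MCC must exceed 0.95.

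**4. What the point estimate needs.** Prevalence of the positive class is not given and differs between the three ASPECTS cut-points, so it is assumed here.
- At 50% prevalence with sensitivity = specificity = s, MCC = 2s − 1. At s = 0.975 this is 0.950. At 40% prevalence the same s gives 0.948.
- With 500 scans at 50% prevalence and errors split evenly, 12 discordant scans give (244² − 6²)/250² = 0.952, and 14 give (243² − 7²)/250² = 0.944.

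Even the point estimate clears 0.95 only with about 2.4% discordance or less (12/500). The confidence limit demands more.

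**5. Chance of meeting the criterion.** Simulation with 20,000 replicates, equal marginals for software and expert, and lower limit = MCC − 1 − 1.645 × SE, with the SE taken from the simulation. Ranges cover assumed prevalences of 30% and 50%. The larger n is roughly the whole patient pool available to the study.

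| True software MCC against the expert | n = 500 | n = 6600 |
|---|---|---|
| 0.44, 0.60, 0.80, 0.90 | 0.00 | 0.00 |
| 0.95 | 0.03–0.04 | 0.05 |
| 0.97 | 0.55–0.66 | 1.00 |
| 0.98 | 0.92–0.94 | 1.00 |

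Below 0.95, more scans do not help, because the obstacle is the reference and not the precision.

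**The case against.** The strongest reply is that an expert MCC of 1 is an inference. The MCC paragraph does not say what the counts are taken against. The general rule lists sensitivity, specificity, predictive values and accuracy, not MCC, and adds that other tests are described in later sections. The MCC test is offered for comparison with earlier work that used an independent standard, and the item that follows uses a follow-up standard. An independent reference may therefore have been intended.

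That stands as a statement about intent, but it does not rescue the text. No section attaches an independent reference, a second reader or a leave-one-reader-out scheme to this test. Either the general rule applies and the criterion is the one derived above, or the reference is undefined. Both need correcting.

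The importance is also limited. Diagnostic accuracy statistics are the plan's principal method. Outcome 1 has its own Bland-Altman criterion of ±2 points. The 494 figure sets only a minimum, since every available scan will be processed.

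A reader might infer three stronger things that the document does not support:
- That 0.44 is the plan's expected software–expert MCC, so that the shortfall from 0.95 can be forecast. It is a result from 34 patients against diffusion MRI, in a study that the plan says was powered on ASPECTS regions, an approach it concedes may be flawed.
- That 97.5% sensitivity and specificity would pass. Under the assumed prevalence they bring only the point estimate to about 0.95.
- That the test is bound to fail. It can pass if agreement is close enough to perfect, roughly an MCC of 0.97 or more, but passing would answer a different question.

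**Conclusion.** The point holds in this form: the non-inferiority test names no reference for its two MCCs, and the only rule in the plan that could supply one makes the expert's MCC equal to 1. The criterion is then a lower 90% limit above 0.95, which tests near-perfect agreement and cannot show that software is no worse than experts. It does not match the 0.44 versus 0.38 basis of the sample size.

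The value of 1 and the 0.95 threshold follow exactly once the two sections are combined. They depend on no assumed prevalence. The pass probabilities and discordance counts do rest on the assumed prevalences and equal marginals, and they illustrate scale only. The Bland-Altman, Wilcoxon, K-alpha and cut-point accuracy analyses under primary outcome 1 are not affected.

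**What to change.** Choose one of two routes before unblinding.

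(a) Keep the test and name one common independent reference for both MCCs, software and baseline expert. The follow-up expert opinion already specified for primary outcome 2 is a candidate. State the binary target and which patients have the reference. Use a paired 90% confidence interval for the difference, since software and expert read the same scans, and write the margin as 0.05 on the MCC scale. Acknowledge the price: against that reference the test concerns detection of ischaemia, not an ASPECTS cut-point, so it moves towards outcome 2.

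(b) Keep outcome 1 on ASPECTS, report the software-versus-expert MCC descriptively at each stated cut-point, and drop the non-inferiority claim.

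Route (b) costs wording only. Route (a) costs wording and a paired interval, for example by bootstrapping scans. It should need no new reading if the outcome 2 reference is used, because the plan already relies on it. Under either route, Sample size considerations should say that the 494 figure comes from a comparison against diffusion MRI and state how far it still applies.

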## Introduction

Accurate and rapid identification and quantification of CT imaging features indicative of early ischaemic and haemorrhagic stroke is required to correctly triage patients for urgent treatment. However, early ischaemic brain changes can be subtle on non-enhanced CT (NECT) and identification requires training and experience^1^. The Alberta Stroke Program Early CT Score (ASPECTS) helps quantify early ischaemia on CT and may aid decision making prior to thrombolysis and thrombectomy^2^–^4^. It is particularly important to exclude acute intracranial haemorrhage as the cause of stroke prior to thrombolytic therapy since thrombolysis may worsen haemorrhage. Additionally, a CT angiogram (CTA) may be required immediately after NECT to identify patients with arterial obstruction who are suitable for thrombectomy. Interpretation of CTA also requires training and experience.

A potential solution to help interpret brain CT and CTA after suspected stroke is offered by e-ASPECTS and e-CTA diagnostic software (Brainomix Ltd, Oxford UK). This software, developed using machine learning, includes an automated ASPECTS and detection of acute haemorrhage on NECT, and a CTA assessment to detect large vessel obstruction (LVO) and collateral blood supply. e-ASPECTS is said to be as accurate as expert human rating of ASPECTS^5^,^6^, and the software has been promoted to support and accelerate stroke treatment decisions. However, as is the case with many diagnostic tools developed using machine learning^7^, e-ASPECTS lacks independent demonstration of reliability, safety or clinical utility, especially for newer features of haemorrhage detection and CTA assessment^8^. It is also unclear how e-ASPECTS handles other pathologies which make up around 20% of patients presenting with stroke-like symptoms (i.e. stroke mimics) such as tumours, subdural haematomas or infections.

The Real-world Independent Testing of e-ASPECTS Software (RITeS) study will independently evaluate the accuracy, reliability and clinical benefit of e-ASPECTS and e-CTA software. Here we pre-specify the statistical analysis plan for RITeS.

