### Primary outcomes

1. Difference in ASPECT scores provided by e-ASPECTS versus expert human readers.2. Diagnostic accuracy of e-ASPECTS versus expert human readers for identifying the cause of stroke symptoms (i.e. ischaemia, haemorrhage, other).

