### Tertiary outcomes

**
*1. Haemorrhage quantification by e-ASPECTS versus expert human readers.*
** We will use all RITeS NECT containing acute haemorrhage for this analysis. This includes scans acquired from haemorrhagic stroke trials (i.e. brain haemorrhages with or without intraventricular extension) in addition to scans classed as mimics in ischaemic stroke trials (e.g. subdural or subarachnoid haemorrhages).

Haemorrhage will be quantified by location and extent as follows.

*Haemorrhage location*

Haemorrhage location will be defined by side and gross anatomical regions of the brain affected including cerebral lobes (i.e. frontal, parietal, temporal, occipital), basal ganglia, brainstem, cerebellum, or extra-axial compartment (i.e. intra-ventricular, subarachnoid, subdural, extra-dural). We will convert e-ASPECTS haemorrhage detection overlay to these same 22 (11 per side) categories following visual review, blinded to human-reader results.

We will look at differences in the regions (and their number) identified by expert humans and e-ASPECTS and if the data are amenable, consider using methods that account for multiple concurrent haemorrhage sites per patient^52^.

*Haemorrhage extent*

Haemorrhage extent will require a comparison of haemorrhage volume calculated at the voxel level (e-ASPECTS) and haemorrhage dimensions used to estimate volume (i.e. the ABC/2 score^21^,^53^, human readers). We will use Bland-Altman testing (expected range of agreement to be within ± 10 mm^3^) and K-alpha statistics to test agreement between e-ASPECTS and human-rated results.

**
*2a. Impact of e-ASPECTS on diagnostic confidence and treatment decisions.*
** We will invite stroke and hospital admission physicians with a range of experience to complete an online questionnaire including RITeS NECT and relevant clinical scenarios, similar to previous work conducted by RITeS members^1^,^54^. We will compare responses for readers before and after ASPECTS is calculated (i.e. with and without e-ASPECTS overlay) to assess whether ASPECTS alters confidence in stroke diagnosis and determine its influence on management decisions.

RITeS cases with the following range of relevant radiological findings will be selected: with obvious, subtle and no ischaemic brain lesions (and a range of ASPECTS results); with and without hyperattenuating arteries; with subtle brain and extra-axial haemorrhage; with and without pre-stroke brain changes.

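### Primary outcome 2 is declared by cause, but its third analysis pools every structural cause, so the class *other* gets no accuracy result of its own and a wrong-cause call on a mimic can count there as a hit

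*SAP article*

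**What the plan says.** Under Methods, Primary outcomes, the second outcome is accuracy for "identifying the cause of stroke symptoms (i.e. ischaemia, haemorrhage, other": three named classes of cause.

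Under Statistical analysis, Primary outcomes, item 2, the outcome is split into three comparisons. The first is "Identifying features of ischaemic stroke (including ischaemic lesions in any brain location and/or intracranial hyperattenuating arteries", the second is haemorrhage, and the third is "Identifying any structural causes of stroke symptoms on baseline imaging (including mimics". Software and baseline expert readers are each compared with "human-expert opinion using all available follow-up data including further imaging".

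Scoring comes from Analysis principles and general considerations: "we will calculate true/false positive/negative cases (TP, FP, TN, FN, respectively". The only matching condition there is that "matched results require same score and side". Nothing is said about agreement on the category of cause.

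For non-enhanced CT, the software outputs described in the Introduction and in Analysis principles are an ASPECTS, haemorrhage and arterial hyperattenuation. The Introduction names mimics as an open question: "It is also unclear how e-ASPECTS handles other pathologies".

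**The concern.** The declared outcome asks which cause is present. The third analysis asks whether any structural cause is present. It contains the targets of the first two analyses and adds mimics to them. No accuracy analysis has *other* alone as its target.

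Two things follow. First, the Introduction's question about mimics gets no direct answer from the primary outcome that comes closest to it. Second, the composite can credit a call for the wrong reason. A tumour reported as early ischaemia is abnormal on the index test and abnormal on the reference, so the ordinary binary rule makes it a true positive. Baseline experts did rate structural mimics (Methods, Patient population). In the composite, an expert who reports a tumour and software that reports ischaemia on the same scan would therefore score equally, under a heading about identifying the cause.

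**Working it through.** The plan states no figure on this point, so there is none to reproduce. The check is one of classification, followed by an illustration of size.

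**Step 1. One case through the three analyses.** Take a tumour (reference: other structural cause) that the software reports as ischaemia.

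| Analysis | Reference | Software | Result |
|---|---|---|---|
| 1. Ischaemic features | negative | positive | false positive |
| 2. Haemorrhage | negative | negative | true negative |
| 3. Any structural cause | positive | positive | true positive (generic rule) |

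No mimic output is described, so the software can be positive on a non-haemorrhagic mimic only by calling ischaemia, an abnormal artery or haemorrhage. Each such hit in analysis 3 names the wrong cause.

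**Step 2. Is the gap filled elsewhere?** Table 4 separates mimics, but only for processing success. Table 5, which fixes the accuracy variables and subgroups, has no mimic term. The sensitivity analysis with 26% mimics repeats the same three analyses in a different mix. Analysis 1 counts the tumour as an error but pools it with all other non-ischaemic cases, so the mimic error rate cannot be recovered from it.

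**Step 3. Possible size in analysis 3.** Let m be the mimic share of reference-positives, s the detection rate in ischaemia and haemorrhage with the right cause, and f the share of mimics flagged. Here all mimics are taken to be non-haemorrhagic.

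- Any-cause sensitivity = (1 − m) × s + m × f
- Right-cause sensitivity = (1 − m) × s
- Wrong-cause true positives per 1000 reference-positives = 1000 × m × f

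All inputs are assumptions. The plan says only that the mimic share of the main sample will be far below 26%.

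| m | s | f = 0 (equals right-cause) | f = 0.5 | f = 1 | Wrong-cause hits per 1000, f = 0.5 / f = 1 |
|---|---|---|---|---|---|
| 2% | 0.60 | 58.8% | 59.8% | 60.8% | 10 / 20 |
| 2% | 0.80 | 78.4% | 79.4% | 80.4% | 10 / 20 |
| 5% | 0.60 | 57.0% | 59.5% | 62.0% | 25 / 50 |
| 5% | 0.80 | 76.0% | 78.5% | 81.0% | 25 / 50 |
| 26% | 0.60 | 44.4% | 57.4% | 70.4% | 130 / 260 |
| 26% | 0.80 | 59.2% | 72.2% | 85.2% | 130 / 260 |

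The gain is m × f whatever s is. The planned 26% is a share of the total sample. It equals m only if every patient is reference-positive.

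**Step 4. The penalty in analysis 1.** Assume every non-mimic is ischaemic or haemorrhagic on the reference, with haemorrhage a share h of non-mimics. Mimics then make up m / [m + (1 − m) × h] of the negatives in analysis 1. Calling all of them ischaemic lowers specificity by up to that share.

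- h = 12.4% (SSNAP figure in the SAP): at m = 2%, 0.02 / (0.02 + 0.98 × 0.124) = 14%; at m = 5%, 30%; at m = 26%, 74%.
- h = (947 + 537) / 6612 = 22.4% (haemorrhage studies over the Table 1 total): 8%, 19% and 61%.

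The matching gains in analysis 3 at f = 1 are 2, 5 and 26 percentage points.

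**The case against.** The best defence is that the composite is a legitimate choice. The abstract states the aim as all causes of symptoms, and whether any structural cause was flagged is a useful triage measure. Scoring *other* alone would give the software zero sensitivity on non-haemorrhagic mimics by construction, which teaches little. This stands: the composite need not be replaced.

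Four stronger readings are tempting, and the documents do not support them.

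- **That mimics are never assessed.** They are positives in analysis 3 and negatives in analysis 1. They also appear in Table 4 and drive the 26% sensitivity analysis. What is missing is a separate result.
- **That the plan rewards the error overall.** The same case is a false positive in analysis 1. On the assumptions of Step 4, the specificity lost there exceeds the sensitivity gained in analysis 3. Ischaemic patients without ischaemic features on the reference would reduce that loss.
- **That the plan prescribes credit for a wrong cause.** It does not. The credit is inferred from the generic rule, and the item's heading could be read as requiring the right cause. The fault is an unstated scoring rule.
- **That extra-axial bleeds will be misclassified, or that every flagged mimic is a wrong diagnosis.** Tertiary outcomes does speak of "scans classed as mimics in ischaemic stroke trials (e.g. subdural or subarachnoid haemorrhages", but it includes those scans as haemorrhage, and Table 3 lists extra-axial bleeding under haemorrhage. The reference for this outcome is expert opinion, not the source-trial label. The software can correctly call a subdural or subarachnoid bleed, so the wrong-cause argument is confined to non-haemorrhagic mimics.

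**Conclusion.** The mismatch is real. The outcome is declared by cause, the third analysis is a composite, and no accuracy analysis isolates *other*. Under ordinary binary scoring, every software hit on a non-haemorrhagic mimic in that composite would name the wrong cause. This conclusion rests on two readings of the text: that the generic two-by-two rule applies unchanged, and that the software has no mimic output because none is described.

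The numerical effect is illustrative only, since the documents give neither the detection rate nor the mimic share among reference-positives. With a small mimic share the composite sensitivity moves by a few points at most. With a large one, as the 26% sensitivity analysis is built to have, it could move by tens of points. Analyses 1 and 2 remain valid, and the error is visible in analysis 1, though not attributable to mimics there. This is a should-fix: it does not invalidate the outcome, but as written the outcome does not answer the question it declares.

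**What to change.** 1. Reconcile the declared outcome in Methods with the three analyses under Statistical analysis.
2. Keep the third analysis, labelled as any structural abnormality flagged.
3. Add a cross-table of reference cause (ischaemia, haemorrhage, other structural, none) against called cause, once for the software and once for the baseline expert. Count the cause as identified only when the two agree.
4. Report the proportion of *other* cases called ischaemia, haemorrhage or normal.
5. State that acute extra-axial bleeding counts as haemorrhage for this outcome, in line with Table 3 and Tertiary outcomes.

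The cost is SAP wording and one extra table from data already held. The software's figures may look less favourable.
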